### Prescription for compression stockings

Compression stockings will be prescribed for those participants who are not yet using compressive techniques. Prescription will be based on clinical severity. CEAP C2 to C3 compression of 20–30 mmHg, CEAP C4 to C6 30–40 mmHg compression and, for patients with recurring ulcers, compression of 40–50 mmHg [2]. Compliance (adherence to the use of socks) will be recorded daily in a notebook.

### Strategies to improve adherence to the intervention protocols

After the first session of the exercise program, the participants will receive a follow-up guide containing questions regarding compressive therapy, stretching and lower-limb positioning during rest.

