**Fig. 2 Fig2:**
[figure not shown]
Overview of assessment. Standard Protocol Items: Recommendations for Interventional Trials (SPIRIT) Figure showing the schedule of enrollment, interventions and assessment

All participants will receive educational information regarding the disease, as well as the usual care (hygiene and compressive techniques) and treatments to improve symptoms and quality of life (QOL).

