## Interventions

### Exercise prescription

The exercise program will consist of (1) aerobic training, (2) strengthening, and (3) unsupervised stretching exercises performed at home. The cardiovascular exercises will be performed using a cycle ergometer and the rubber step. The muscle strengthening will be performed using resistive loads for the calf muscles. The participants will receive a written and illustrated guide for performing active stretching exercises of the calf and tibialis anterior muscles once a day for 20 s (each muscle group) at home 24 h after supervision [22]. The exercise program will last ~ 40 min and will be performed twice a week, for a total of 16 sessions. Heart rate (HR) and blood pressure will be checked at the beginning and end of the training, as well as at the end of each series.
Aerobic training
Cycle ergometer exercise

The perceived fatigue of the participants will be measured using the modified 0–10 BORG scale [23], every 5 min. The participants will warm up for 5 min on the cycle ergometer without a load at the beginning of the protocol. Next, the participants will perform the cardiovascular exercises using the cycle ergometer for 15 min. The load will be adjusted at a setting up to moderate intensity (between 4 and 6 of the modified BORG scale 0–10).
b)Bench step-up exercise

The bench step-up exercise will be performed on a rubber step at a height of 20 cm. The participants will be instructed to walk up and down on steps with one foot at a time using free cadence. They will be instructed to perform the movement as fast as possible for a maximal of 12 repetitions and exercise progression (5 to 10 repetitions) will be weekly increased, according to individual tolerance.

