### Health education speeches

All the participants will be invited to attend an educational speech about the disease, risk factors, lifestyle changes and lower-limb care (hygiene, exercises, dressings), as well as the benefits of using compressive techniques. The speeches will be performed (immediately after the first assessment) by a blinded evaluator for each allocation group who will perform the evaluations and reassessments.

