### Conventional treatment for the control group

Conventional treatment will consist of the health education speech, use of prescribed medication, compression stocking and medical guidance. The controls will be instructed to maintain their usual activities and treatments and not perform any type of supervised exercises during the 2 months after their first evaluation.

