#### Quality of life (QOL)

A Brazilian version of the VEINES-QOL (Venous Insufficiency Epidemiological and Economic Study-Quality of Life) questionnaire [29] will be used to assess QOL. This instrument assesses 26 items: 10 symptom-related items, nine items regarding daily-life activities, one item related to the time of the day when the symptoms are more intense, one item regarding the changes due to the disease in the last year, and five questions about the psychological impact of the symptoms/disease. Symptoms, daily-living limitations and psychological impact questions are related to the last 4 weeks. Each domain has a different scale and will be analyzed separately.

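### The guide on compression and leg positioning is tied to the first exercise session, so it probably reaches only the exercise arm although compression is background care in both: a small, avoidable co-intervention difference bearing on QOL

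*Protocol article*

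**What the plan says.** The adherence section gives one measure: "After the first session of the exercise program, the participants will receive a follow-up guide containing questions regarding compressive therapy". The full list of topics is "compressive therapy, stretching and lower-limb positioning during rest".

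The Trial design section assigns the exercise programme to the treatment group. The section on conventional treatment tells controls to avoid supervised exercise for two months and lists their care: "Conventional treatment will consist of the health education speech, use of prescribed medication, compression stocking and medical guidance". No guide appears in that list.

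Compression is meant for everyone:
- The text after Fig. 2 states: "All participants will receive educational information regarding the disease, as well as the usual care (hygiene and compressive techniques".
- Everyone is invited to the education speech, which covers lower-limb care "as well as the benefits of using compressive techniques".
- Stockings are prescribed to any participant not yet using compression, and "Compliance (adherence to the use of socks) will be recorded daily in a notebook". Neither provision is limited to one arm.

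QOL is one of two primary outcomes. On its recall period the QOL section says: "Symptoms, daily-living limitations and psychological impact questions are related to the last 4 weeks".

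**The concern.** The protocol takes care to give both arms the same compression care, and then attaches a further prompt about compression and leg positioning to an event that only one arm has. Stretching belongs to the exercise programme, so a stretching prompt for that arm alone is in order. Compression and leg positioning are not among the programme's components, which are aerobic training, strengthening and home stretching.

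What is at stake is the week-8 QOL contrast. Participants report QOL themselves and know their arm, and most items look back over the preceding four weeks, within the period when any difference in stocking wear would act. If the guide does what its section heading intends, part of any QOL benefit could come from better stocking use and be credited to supervised exercise. No such pathway is claimed for the other primary outcome, calf-muscle endurance.

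**Working it through.** **Who receives the guide**

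1. Trigger: the first exercise session. Only the treatment group does the programme and controls are told not to exercise under supervision, so the trigger never occurs for them.
2. Wording: provisions for both arms (text after Fig. 2; Health education speeches) refer to all participants. The Exercise prescription section uses the plain term, without 'all', for people who are exercising, and the adherence section uses the same plain term.
3. Content: stretching is prescribed only within the exercise programme.
4. Control care: the listed package contains no guide, and no other section gives controls an equivalent.

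One-arm delivery is therefore an inference, but the more natural one. If the guide was meant for everyone, its timing is still fixed to an event that controls do not have.

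**How large the effect could be**

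The document gives no figure to reproduce: no effect of the guide on wear, no effect of wear on QOL, no QOL standard deviation, and no final sample size (this is left to a pilot study). Only the 0.05 significance level comes from the analysis paragraph. All other inputs are assumptions:
- extra stocking wear in the exercise arm: 0 to 0.30 (0 to 30 percentage points);
- effect of wear on a QOL domain score: 0.3 to 0.5 SD;
- participants per arm: n = 20, 30 or 50;
- a plain two-sided, two-sample z test.

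Bias b = wear difference × effect of wear:
- lower end: 0 × 0.3 = 0;
- upper end: 0.30 × 0.5 = 0.15 SD.

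Wear difference needed for b = 0.1 SD: 0.1/0.5 = 0.20 to 0.1/0.3 = 0.33, that is 20 to 33 points. That is a lot to expect from a list of questions.

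Probability of a significant result with no exercise effect, with SE = sqrt(2/n):

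P(Z > 1.96 − b/SE) + P(Z < −1.96 − b/SE)

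| n per arm | SE | b = 0 | b = 0.15 |
|---|---|---|---|
| 20 | 0.316 | 5.0% | 7.6% |
| 30 | 0.258 | 5.0% | 9.0% |
| 50 | 0.200 | 5.0% | 11.7% |

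The last column needs both the wear difference and its effect at their upper ends. It is a ceiling under these assumptions, not a forecast.

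**What the stocking notebook could show**

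With 30 per arm and an assumed SD of 30 points in percent of days worn, the 95% confidence interval for the difference between arms has half-width 1.96 × 30 × sqrt(2/30) = 15.2 points (10.1 with an SD of 20; 20.2 with an SD of 40). The notebook would show a large difference in wear but not a small one.

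**The case against.** - **Delivery is inferred.** The text does not restrict the guide to the treatment group, and a condensed article may omit who gets which handout. This stands as a caution, and it is why the point is worded as the more natural reading. It does not remove the point, because the one timing the article does state cannot apply to controls.
- **The guide's function is unclear.** It is described only as containing questions. It could be a self-monitoring checklist, or even the daily stocking record, on top of a speech, a prescription and a notebook that are not limited by arm. This stands: any difference is an increment and may be negligible.
- **The figures are assumed.** They also come from a simple z test, whereas the plan is a mixed model with age and body mass index as covariates. This stands as well, and the figures only bound what is plausible. The planned model changes the standard error, but with stocking wear not among its covariates it would not remove a bias from wear. Adjusting for wear measured after randomization would not be a clean remedy.
- **A comparison of packages is legitimate.** Adherence support may be part of a programme, and the supervised exercise, which "will be performed twice a week, for a total of 16 sessions", separates the arms far more than one sheet does. The second part stands: removing the guide difference does not leave exercise as the only contrast. The first part fits poorly with a protocol that otherwise gives both arms the same compression care and states its hypothesis about a muscle-training programme.

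**Conclusion.** The concern holds as a minor one, worth considering. Followed as written, the protocol most naturally gives the exercise arm alone an extra prompt about compression and leg positioning, neither of which is part of the exercise programme. Any resulting bias would favour exercise on QOL. Its size is not derivable from the document and may be zero; 0 to 0.15 SD is the range under the assumed effects on wear and QOL, and values near the top need a larger change in wear than a list of questions is likely to produce. Confidence is medium, because one-arm delivery is inferred and the guide's function is not described. The case for acting is that the difference is avoidable at almost no cost.

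**What to change.** Hand the compression and leg-positioning part of the guide to all participants at the education speech, which is scheduled immediately after the first assessment. The evaluator gives that speech, but a handout identical for everyone reveals nothing about allocation. Keep only the stretching part for the exercise arm after its first session. Report stocking wear from the notebook by arm beside the week-8 QOL result, with its confidence interval.

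If the guide is to stay in the exercise arm only, say so in the adherence section and describe the tested intervention as supervised exercise plus support for compression adherence.

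The cost is one handout for controls at a contact they already have and one or two sentences of wording. No visit, sample size or model term changes. The small downside is that controls receive slightly more than their usual care.

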### Conventional treatment for the control group

Conventional treatment will consist of the health education speech, use of prescribed medication, compression stocking and medical guidance. The controls will be instructed to maintain their usual activities and treatments and not perform any type of supervised exercises during the 2 months after their first evaluation.

## Outcomes

### Primary outcome

#### Assessment of calf-muscle endurance

The external cadence heel-raise test [26] adapted to the bipodal position [27] will be used to assess calf-muscle endurance. Calf-muscle endurance will be assessed by the number of repetitions achieved during the test. The participants will be instructed to remain in an orthostatic position, barefoot with bipodal support. Their balance will be maintained through contact of the fingertips of the dominant hand on a wall with elbows flexed at 90°. Next, the participants will be asked to raise their heels from the floor. The evaluator will record the maximum height reached by the participant using a stadiometer and will explain to the participants that they should achieve the marking with their heads during the heel-raise movement. The cadence of the test will be determined by a metronome (46 beats per minute) and they will be encouraged to perform as many heel-raise movements as possible. The test will be interrupted in the following situations: if the participant does not reach maximum elevation on two consecutive occasions; transfers too much weight against the wall on two consecutive occasions; performs knee flexion on two consecutive occasions; or asks to interrupt the test [28]. Blood pressure and HR will be monitored at rest, immediately after the test and after a resting period post test.

#### Quality of life (QOL)

A Brazilian version of the VEINES-QOL (Venous Insufficiency Epidemiological and Economic Study-Quality of Life) questionnaire [29] will be used to assess QOL. This instrument assesses 26 items: 10 symptom-related items, nine items regarding daily-life activities, one item related to the time of the day when the symptoms are more intense, one item regarding the changes due to the disease in the last year, and five questions about the psychological impact of the symptoms/disease. Symptoms, daily-living limitations and psychological impact questions are related to the last 4 weeks. Each domain has a different scale and will be analyzed separately.

### Secondary outcomes

#### Assessment of exercise capacity

The step test (ST) will be used to assess exercise capacity and will follow the recommendations previously published [30]. It will last for 6 min (Step test 6; ST6), and the values ​​for HR, systemic arterial pressure, dyspnea score using the modified BORG scale (0–10) and oxyhemoglobin saturation using a digital oximeter (SpO_2_%) will be registered at baseline and after the test. The number of steps will be used to analyze the participant climbing up and down (one cycle of climbing up and down was counted as one step). A 20-cm-tall rubber step will be used and the patient will be advised to wear comfortable clothing and shoes. The examiner will initially demonstrate how to perform the test. The subject should start the test using the right leg, followed by the left leg. To go down the step, the participant must follow the same order; first the right leg followed by the left leg, and then repeat the sequence at the given time. The participant will be instructed to perform the test as quickly as possible with free cadence and without discomfort. The test will be discontinued if the HR exceeds 85% of age-predicted maximal HR [31], if the participant points to a value greater than 7 on the modified BORG scale, or if the participant asks on their own initiative to finish the activity. If the participant reports fatigue or dyspnea they will be instructed to stop the test and rest on a chair. They will also be instructed to continue the test as soon as possible. During the resting period, the timer on the stopwatch will continue and the examiner should record the break. The patient will be verbally encouraged every minute without excess stimulation. The examiner will warn the subject with a clear “stop” message when 15 s are left. The same vital signs and symptom scores will be evaluated at the end of the test.

#### Ankle range of motion

The joint movement range will be measured using a simple goniometer. The measurements will be standardized for all the patients in a sitting position with knees extended and ankles initially at 90°. One arm of the goniometer will be positioned over the lateral malleolus, while the movable arm will be positioned over the fifth metatarsal accompanying the entire ankle range for dorsiflexion and flexion-extension [32].

#### Electrical activity assessment

During the tests (external cadence heel-raise test and the step test), electrical activity of the calf and tibialis anterior muscles will be assessed using superficial electromyography (SEM). The electrodes will be placed according to Surface ElectroMyoGraphy for the Non-Invasive Assessment of Muscle (SENIAM) guidelines for Surface ElectroMyoGraphy (SEMG) placement [33]. For the medial portion of the gastrocnemius muscle, the electrodes will be placed on the most prominent bulge of the muscle. For the tibialis anterior muscle, the electrodes will be placed at one third of the line between the tip of the fibula and the tip of the medial malleolus. A signal-conditioning module (TeleMyo DTS desk Receiver®, Noraxon USA Inc., Scottsdale, AZ, USA) with four wireless sensors (Clinical DTS-Noraxon®, Noraxon, Scottsdale, AZ, USA) will be used. The signals will be captured and stored using the MR 3.8 software (Noraxon USA Inc., Scottsdale, AZ, USA). The mean peak will be used to normalize the electrical signal [34], and the electromyographic signal will be analyzed at four moments (25%, 50%, 75% and 100%).

#### Cardiac output assessment

A non-invasive registering of cardiac output will be performed by a cardiograph through electrical impedance using the PhysioFlow® Q-Link equipment (Paris, France). This method has been shown to be valid and reliable at rest and during submaximal exercise in patients with normal cardiorespiratory function [35]. The skin preparation and placement of the electrodes will be according to the manufacturer’s recommendations. Following trichotomy, alcohol cleansing and abrasion with Nuprep® gel (Weaver, Aurora, CO, USA), six transcutaneous electrodes (PhysioFlow PS-50, Manatec Biomedical, Macheren, France) will be placed on the patient’s upper region. Next, two emitting electrodes will be placed on the left base of the neck, above the supraclavicular fossa and two sensing electrodes will be placed below the xiphoid process on the right side of the patient. During the functional tests, the two sensing electrodes will be positioned in the paravertebral area, at the level of the xiphoid process. One electrode will be located in the middle of the sternum and the other at the left lateral chest wall (sixth intercostal space) to conduct the electrocardiogram signal.

### Sample size

The sample size will be calculated based on a pilot study with eight patients (four patients in each group) using a multivariate analysis of variance (manova) test with repeated measures, within-between interaction with two groups and two measurements by analyzing calf endurance and the standard deviation of the number of repetitions from the pilot study. A two-tailed alpha error of 0.01 will be considered with a power of 80% considering clinical improvement for subjects with chronic venous disease after the supervised exercise protocol. The effect size will be calculated at the end of the protocol considering the number of repetitions of the calf-endurance test of all study participants. Moreover, considering a 20% loss to follow-up and 5% missing data, the number of participants will be increased by at least 20% based on sample size. The GPower (Germany) version 3.1 program will be used for statistical analysis.

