**Methods/design:**

This is an evaluator-blind, randomized clinical trial with an 8-week duration and a follow-up evaluation at week 16. A pilot study with subjects with a CVI diagnosis will be performed to calculate sample size. The participants will be randomly allocated (1:1) into a treatment or a control group (usual care/no intervention). The treatment intervention consists of a bi-weekly supervised exercise program of the lower limbs that will include aerobic training, strengthening and cardiovascular exercises. The participants from both groups will participate in a health education lecture. Primary outcomes are changes in calf-muscle endurance and QOL score. Secondary outcomes are changes in exercise capacity, ankle ROM, electrical muscle activity and cardiac output. The first statistical comparison will be performed after 8 weeks’ intervention.

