### Hypotheses

We hypothesize that a supervised lower-limb muscle-training program in participants with CVI will improve calf-muscle endurance and QOL scores.

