### Trial design

The evaluations will start in January 2020. After evaluation, participants will be randomly allocated to two evaluator-blinded groups: the treatment group (TG) and the control group (CG). The randomization.com program will be used to randomize the participants and stratification will be performed to ensure balance between the groups within two strata (Clinical, Etiology, Anatomical, Pathophysiology (CEAP) 2 and 3 and CEAP 4 to 6). A separate, blinded researcher will contact the participants by telephone to ensure allocation concealment during screening, consent and initial assessment. A study researcher responsible for implementation will apply the exercise program.

Patients in the TG will perform the exercise program as described in this protocol and will start 1 week after the initial evaluation. The patients in the CG will continue their usual treatments (medication use, compression stockings and medical guidance). After 8 weeks of intervention, the patients will be re-evaluated (using the same initial evaluation questionnaire) by the same blinded evaluator for each group. The primary outcomes will be calf-muscle endurance and QOL and the secondary outcomes will be exercise capacity, ROM electrical muscle activity, and cardiac output. A final reassessment will be performed 8 weeks after the re-evaluation, as shown in Figs. 1 and 2 (Standard Protocol Items: Recommendations for Interventional Trials (SPIRIT) Figure).

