The statistical analysis will be performed using the GraphPad Prism version 5.0 statistical package software (GraphPad Software Inc., San Diego, CA, USA). The results of patient baseline characteristics and outcome variables (both primary and secondary) will be summarized using descriptive summary measures: expressed as mean (standard deviation) or median (range) for continuous variables and *n* (%) for categorical variables. The sample normality will be tested by the Shapiro-Wilk test. Treatment effects or differences between the study groups for primary and secondary outcomes will be analyzed by linear mixed model for group (usual care versus intervention) and time (baseline, 8 weeks and 12 weeks). As linear mixed models use all available data at each time point, no missing data imputation will be performed. Age and body mass index (BMI) will be included as covariates by adding them to the regression model. The clinical classification CEAP will be included as covariate if randomization imbalance occurs. The analyses will be based on the intention-to-treat principle, including data of all randomized participants with at least one outcome measure. The significance level will be set at 95% (*p* < 0.05). All participants will be included in the analysis of the original groups following the Consolidated Standards of Reporting Trials (CONSORT) recommendations.

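### The trial is sized at two-sided alpha 0.01 but tested at 0.05, and two primary outcomes share that 0.05 without a stated success rule

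*Protocol article*

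**What the plan says.** **Sizing.** The Sample size section states: "A two-tailed alpha error of 0.01 will be considered with a power of 80" percent. The calculation is a repeated-measures within-between interaction with two groups and "two measurements by analyzing calf endurance and the standard deviation of the number of repetitions from the pilot study". QOL does not enter it. No sample size, effect size or standard deviation is given, because these are to come from an eight-patient pilot.

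**Testing.** The statistical paragraph of the Data collection, management and analysis section applies one linear mixed model to primary and secondary outcomes and sets a single level for all of them: "The significance level will be set at 95% (*p* < 0.05"). It does not refer back to 0.01.

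**Primary outcomes.** Trial design says "The primary outcomes will be calf-muscle endurance and QOL", and the abstract says "Primary outcomes are changes in calf-muscle endurance and QOL score". The Quality of life (QOL) section adds, on the questionnaire: "Each domain has a different scale and will be analyzed separately".

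**Success.** The Hypotheses section expects that the programme "will improve calf-muscle endurance and QOL scores". No section says whether a positive trial needs one of these outcomes or both.

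**The concern.** There are two separate faults.

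First, the article gives two decision thresholds for the same outcome. If calf endurance gives p = 0.03 at week 8, the trial is negative at the level it was sized for and positive at the level in the analysis paragraph. Whoever reports the result can choose after seeing it. The stated 80% power also belongs to a test that the analysis paragraph does not run.

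Second, two primary outcomes are each given the whole 0.05. If a favourable result on either can be claimed as success, the chance of at least one false claim exceeds 5%. Separate QOL domain tests add further chances, and the article does not fix how many. If instead both outcomes must succeed, the error rate is sound, but the sample size was built for only half of the claim.

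**Working it through.** **Inputs from the article:** sizing alpha 0.01 two-sided; power 80%; analysis level 0.05 (sidedness not stated, taken as two-sided); two primary outcomes; sizing on calf endurance only.

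**Assumptions:** normal approximation; a single contrast between arms (with two groups and two measurements the interaction has one degree of freedom); correlation between the primaries from 0 to 0.9; number of QOL domain tests. There is no planned sample size to reproduce, so only the error rates can be worked with.

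**1. Power when sized at 0.01 and tested at another level.**
Sizing fixes the expected test statistic at z(0.995) + z(0.80) = 2.576 + 0.842 = 3.417. Power at level α is Φ(3.417 − z(1−α/2)).

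| Level of the test | Calculation | Power, calf endurance |
|---|---|---|
| 0.01 | Φ(3.417 − 2.576) | 80% |
| 0.025 | Φ(3.417 − 2.241) | 88.0% |
| 0.05 | Φ(3.417 − 1.960) | 92.8% |

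This does not depend on the effect size. As a cross-check with whole patients, at assumed standardised differences of 0.5, 0.8 and 1.0 the 0.01 design needs 94, 37 and 24 per arm. Power is then 0.929, 0.931 and 0.934 at 0.05, and 0.882, 0.885 and 0.889 at 0.025. These sample sizes are illustrations, not figures from the plan.

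**2. Cost in patients.** The ratio of sample sizes, 0.01 against 0.05, is (3.417 / (1.960 + 0.842))² = 1.49. If 0.05 was the intended level, about 1 − 1/1.49 = 33% fewer patients would give 80% power for calf endurance.

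**3. Family-wise error if either primary suffices.** For independent outcomes it is 1 − 0.95² = 9.75%. For correlated outcomes it is one minus the bivariate normal probability that both statistics lie within ±1.96:

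| Correlation (assumed) | Family-wise error at 0.05 each | Ratio to 5% |
|---|---|---|
| 0 | 9.75% | 1.95 |
| 0.3 | 9.5% | 1.90 |
| 0.5 | 9.1% | 1.81 |
| 0.7 | 8.3% | 1.67 |
| 0.9 | 7.0% | 1.41 |

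**4. If QOL domains are tested one by one.** With k independent tests in all, the error is 1 − 0.95^k: 14.3% for k = 3, 18.5% for k = 4 and 26.5% for k = 6. The article does not state the number of domains. It lists five groups of items (10 + 9 + 1 + 1 + 5 = 26), so k = 6 would apply if each group were a domain. Positive correlation would lower these figures.

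**5. If both primaries must succeed.** The chance of a false joint claim is at most 5%, so nothing is inflated. Joint power cannot exceed the smaller of the two powers, and the one for QOL is unknown: the article gives no QOL effect, standard deviation or power.

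**6. Under a corrected rule.** At 0.025 each, the family-wise error is 1 − 0.975² = 4.94% if independent and at most 5% in any case. At 0.01 each it is 1 − 0.99² = 1.99%, with power for calf endurance at 80%.

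**The case against.** The strongest reply is that sizing at a stricter level than the test is conservative. That stands as far as it goes. The sizing alpha does not change the type I error of a test run at 0.05; it only makes the trial larger and raises power for calf endurance. A reader might infer that the mismatch itself makes a false positive about twice as likely. It does not. The near-doubling comes only from two primaries at 0.05, and it is measured against 5%, not against 0.01.

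A second reply is that either-suffices is not written down. This also stands. The Hypotheses section joins the outcomes with 'and', and under a both-required rule there is no inflation. But that sentence states an expectation, not a decision rule, and the both-required reading exposes the unsized QOL outcome.

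A third reply is that a multiplicity rule may sit in an analysis plan that is not shown. The absence of such a rule alone would indeed be no finding. However, the article fixes 0.01 in one section and a flat 0.05 for all outcomes in another, so an analysis plan could cure this only by overriding the article's own text. The 0.01 may have been meant as an allowance for multiplicity, but the article does not say so, and the analysis paragraph does not use it.

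**Conclusion.** The contradiction between 0.01 and 0.05 is certain and needs no assumption. Its effect is that the stated alpha and power do not describe the planned test (about 93% power for calf endurance at 0.05, not 80%), and that any p-value between 0.01 and 0.05 has two possible readings.

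The multiplicity point is conditional. If either primary supports a claim, the family-wise error is about 7% to 9.75% for two tests, with the correlation assumed, and can be higher if QOL domains are tested separately. If both are required, the error is controlled and the gap is joint power.

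Two stronger conclusions are not supported. Loss of error control cannot be blamed on the sizing level. Nor can it be said that splitting alpha costs no patients for the trial as a whole: the 88% at 0.025 covers calf endurance only, and no planned sample size exists to check QOL against.

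**What to change.** 1. State one alpha for the primary analysis and use it in both sections, or say in the Sample size section why a stricter level is used for sizing.
2. Name one VEINES-QOL score as the primary QOL measure. Without this, no two-test rule can be applied.
3. State whether a positive trial requires one or both primaries at week 8.
4. If one suffices, use Holm (smaller p-value against 0.025, then the other against 0.05) or 0.025 for each.
5. If both are required, test each at the full level and size the trial for QOL as well.
6. Describe the other QOL domains, the other time points and the secondary outcomes as supportive.

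This takes a few sentences. It should be settled before the pilot-based sample size is calculated and before any comparison between arms is seen. The cost is a slightly stricter threshold than 0.05 when one primary suffices. Calf endurance keeps about 88% power at 0.025 as long as sizing stays at 0.01; if sizing is restated at 0.025, power returns to 80% with a sample smaller by a factor of (3.417 / (2.241 + 0.842))² = 1.23. Power for QOL cannot be stated from the article and would need its own effect and standard deviation.
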